### Interventions

3.5

*Family Navigator Plus (FN+).* See section 2.2.3.

*Civic Engagement.* Civic engagement—activities intended to address public issues and strengthen communities—was selected as the attention control condition. It mirrors the structure and format of FN+, providing foster parents with equivalent time, attention, knowledge, skills, and confidence-building opportunities, but focuses on youth civic engagement rather than mental health. Session 1 introduces the program and family navigator, defines civic engagement within a developmental framework, and guides foster parents in discussing their child's developmental level, strengths, and opportunities for civic participation. Session 2 focuses on identifying developmentally appropriate civic activities and strategies to initiate and support youth involvement. Session 3 emphasizes goal setting, age-appropriate engagement strategies, collaboration with caseworkers, and structured problem-solving to address barriers to participation. Session 4 supports foster parents in setting developmentally appropriate civic engagement goals while strengthening active listening and validation skills to promote youth autonomy. The final session trains foster parents to locate, evaluate, and use high-quality online civic engagement resources to sustain ongoing involvement. Table 2 provides an overview of civic engagement program components.

**Table 2 tbl2:** Civic engagement program components.

**Session 1**	Understanding Your Child's Developmental Stage	Provide an overview of typical child development and developmentally appropriate civic engagement behaviors
**Session 2**	Initiating Youth Civic Engagement	Discuss developmentally appropriate methods to promote youth civic engagement.
**Session 3**	Promoting Youth Civic Engagement	Build parent capacity to support developmentally appropriate civic engagement.
**Session 4**	Understanding the “why" of civic engagement	Describe the elements of civic engagement that support youth development.
**Session 5**	Using online tools at home	Train parents to find, evaluate, and use online tools to support civic engagement

### Measures

3.6

We plan to use the same measures piloted in the open trial (see Section 2.2.4).

### Monitoring of intervention integrity

3.7

Intervention integrity will be assessed by reviewing 10% of randomly selected audio recordings of FN+ and CE sessions. To increase adherence, family navigators will be provided with a list of allowed and disallowed interventions in each condition. They will also fill out and self-reported adherence checklist at the end of each session. Finally, all family navigators will meet weekly with the PIs to ensure fidelity to the interventions.

### Statistical analysis

3.8

#### Primary outcome

3.8.1

The primary outcome for this study is parent activation. We will examine change in foster parent activation on the P-PAM-MH from baseline to subsequent time points in the intervention, relative to the attention control condition. Foster parent activation will be measured using the P-PAM-MH. Data will be analyzed using two parallel analytic methods: (1) a 2 (Condition) x 3 (Time) repeated measures ANOVA, and (2) a corresponding 2 x 2 repeated measures ANCOVA (using Baseline as a covariate). The ANOVA model evaluates contrasts in actual outcomes, and the ANCOVA model evaluates adjusted mean contrasts, statistically equating groups on baseline status (thus correcting possible group differences at Baseline, and as is often the case, increasing statistical power using baseline as a covariate). We will conduct preliminary analyses to test for additional covariates such as level of education. For the ANOVA model, in addition to time (*df* = 2) and group by time effects (*df* = 2), pairwise contrasts of outcomes at the 3 times will be conducted on the time factor. In addition to overall treatment group effects, treatment groups will be contrasted on average P-PAM-MH within times, and on change between Baseline and the two post-baseline time points. For the ANCOVA models, groups will be contrasted on the adjusted mean average across all times, on adjusted means at each post-baseline time, and on the difference between the 2 post-baseline adjusted means.

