### Design overview

3.1

Phase III includes a 5-week, single site pilot feasibility RCT of the FN + program as compared to a civic engagement attention control condition (CE). The attention control condition was designed to serve as a rigorous comparison group by providing foster parents with equivalent time, attention, knowledge, skills, and confidence-building opportunities as the treatment condition, but focused on youth civic engagement rather than mental health. By matching structure and intensity while differing in content, any observed differences in outcomes between groups can be attributed to the mental health–specific components of the FN + intervention. Primary and secondary outcomes are assessed after the 5-week intervention, and at 3-month follow-up. All study procedures are approved by the institutional and Illinois DCFS Institutional Review Boards. The trial is registered on clinical trials.gov (NCT06978959).

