### Randomization

3.4

Following eligibility determination, participants will be randomized 1:1 to either the intervention (FN+) or attention control condition (CE), stratifying for age of child. Three developmentally informed strata will be used: early childhood (5–9 years), middle childhood/early adolescence (10–13 years), and middle/late adolescence (14–17 years). These strata were selected to reflect clinically meaningful differences in mental health symptom presentation, predominant treatment modalities offered, age-related considerations related to care navigation and decisional autonomy. Stratified block randomization (block size of three) will be implemented within each age stratum, using a pre-generated allocation sequence held by a study team member not involved in enrollment, to maintain balance across the two conditions within strata.

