#### Power analyses and sample size considerations

3.8.3

Effect sizes yielding 80% power were estimated based on a sample size of 60 subjects, and assuming a type 1 error rate of α = .05, and assuming a sphericity correction of ε = 0.75 for 2 *df* mixed ANOVA models, and an average correlation between all repeated measures of *r* = .5 for all models. Tests of the overall 2x3 mixed ANOVA interaction achieved 80% power at an f-ratio effect size of *f* = 0.184 (i.e., partial η2 = .0327), and interaction tests of contrasts of pairs of times had 80% power for effect size *f* = 0.184 (i.e., pη2 = .0327). ANCOVA models include baseline as a covariate and predict subsequent outcome variance. With respect to predictions at a single post-baseline assessment, 80% power is present to detect an effect size of partial *f* = 0.368 (i.e., pη2 = .119). Both detectable effect size estimates rely strongly on assumptions about error structure. The pilot data will provide new error structure information (within the context of the models above) that will improve future power estimates for a broader RCT. Although this study is not adequately powered to detect small effects, we will generate data sufficient to better inform future power analyses with respect to error structure and effect sizes.

Consistent with NIH guidance for R34 pilot and feasibility studies, the sample size was selected to evaluate feasibility, acceptability, recruitment procedures, and preliminary signals of effect, rather than to definitively test efficacy. Accordingly, the effect sizes reported above reflect the minimum effects detectable at the predetermined feasibility-based sample size, not the effects the current study is powered to confirm. Age stratification (5–9, 10–13, and 14–17 years) will be used to maintain balance on a clinically important developmental variable while preserving the overall sample size. Because the study is not powered to detect age-stratum-specific effects, age will be examined descriptively and included as a covariate in exploratory sensitivity analyses. Pilot data, including stratum-specific variance and correlation estimates, will be used to refine sample size estimates for the subsequent definitive RCT.

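### The primary outcome is analysed by two unranked parallel models with 11 between-arm tests, and no model, contrast or visit is named as primary

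*Protocol article*

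**What the plan says.** Section 3.8.1 of the protocol article names parent activation as the primary outcome and states: "Data will be analyzed using two parallel analytic methods". The two methods are a 2 (condition) x 3 (time) repeated measures ANOVA and a 2 x 2 repeated measures ANCOVA with baseline as covariate. The section notes that the ANCOVA corrects chance baseline differences and often has more power, but it ranks neither method above the other.

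For the ANOVA it lists the group-by-time effect and the overall group effect, and adds that "treatment groups will be contrasted on average P-PAM-MH within times, and on change between Baseline and the two post-baseline time points". For the ANCOVA, "groups will be contrasted on the adjusted mean average across all times, on adjusted means at each post-baseline time", and also on the difference between the two post-baseline adjusted means.

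Section 3.1 does not choose between the visits: "Primary and secondary outcomes are assessed after the 5-week intervention, and at 3-month follow-up". The second aim in section 3.2 is to test efficacy on parental activation, with a directional hypothesis. Section 3.8.3 gives the only error rate, "assuming a type 1 error rate of α = .05". It also says that the sample size was set by feasibility and that the pilot looks for early indications of effect, not a definitive efficacy result.

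**The concern.** One outcome and one hypothesis lead to 11 between-arm tests of equal standing. If some are significant and others are not, the plan does not say which one answers the second aim. A reader of the results could not tell whether the reported test was chosen in advance or chosen because it came out well.

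This matters in a pilot too. Section 3.8.3 says that the data will inform effect sizes for a later trial. An estimate picked because it was the significant one among several is biased upward, and that bias would pass into the next sample size.

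Two of the listed tests also do not fit the hypothesis. A between-arm comparison at baseline tests only the randomisation. The ANOVA group main effect averages in a visit that precedes randomisation, so it dilutes any treatment effect.

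**Working it through.** **Inputs from the document.** Section 3.8.3: "Effect sizes yielding 80% power were estimated based on a sample size of 60 subjects", α = .05, correlation between repeated measures r = .5, sphericity correction ε = 0.75. Section 3.4: "participants will be randomized 1:1 to either the intervention (FN+) or attention control condition (CE), stratifying for age of child", hence 30 per arm.

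**The plan's own power figures reproduce.**
- 2 x 3 interaction at f = 0.184: λ = f²·N·m·ε/(1 − r) = 0.033856 × 60 × 3 × 0.75 / 0.5 = 9.14, with 1.5 and 87 df. Power is 80.2%.
- Interaction for a pair of times at f = 0.184: λ = 0.033856 × 60 × 2 / 0.5 = 8.13, with 1 and 58 df. Power is 80.0%.
- ANCOVA at one visit, f = 0.368: λ = f²·N = 0.135424 × 60 = 8.13, with 1 and 57 df. Power is 80.0%.

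**Counting the between-arm tests.** The ANOVA has overall group (1), group by time (1), groups within each time (3) and change from baseline (2), which makes 7. The ANCOVA has adjusted average (1), each post-baseline visit (2) and their difference (1), which makes 4. The total is 11. Three of these do not directly test benefit: the baseline contrast, the group main effect that includes baseline, and the difference between the two post-baseline adjusted means. That leaves 8.

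**False-positive rate.** All tests were simulated under no effect: 40,000 trials per scenario, 30 per arm, normal data, no dropout, each test at .05, Greenhouse-Geisser correction for the interaction. Each single test rejected in 4.7% to 5.1% of trials. The chance of at least one rejection was:

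| Set of tests | r = .5 | r = .3, r = .7, AR(1) |
|---|---|---|
| All 11 | 22.0–22.3% | 22.2%, 21.9%, 21.9% |
| 10, without the baseline contrast | 20.6–20.9% | 20.7%, 20.7%, 20.4% |
| 8 that bear on efficacy | 17.8–18.2% | 17.7%, 18.2%, 16.9% |
| Interaction or ANCOVA average | 8.1–8.3% | 8.6%, 8.0%, 8.1% |

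If the 11 tests were independent the figure would be 1 − 0.95^11 = 43.1%. They are strongly correlated, so that is only an upper reference.

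**Disagreement between the models.** The document gives no expected effect, so a sustained effect d (in SD units, equal at both post-baseline visits) is assumed, with r = .5. The value 0.64 corresponds to the plan's detectable ANCOVA effect: 2 × 0.368 × √0.75 = 0.64.

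| d | Interaction vs ANCOVA average | Change score vs ANCOVA, both at post-intervention |
|---|---|---|
| 0 | 7% | 5% |
| 0.3 | 24% | 14% |
| 0.5 | 32% | 19% |
| 0.64 | 24% | 17% |
| 0.8 | 10% | 9% |

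At d = 0.5 the interaction was significant in 48.7% of trials, the ANCOVA average in 75.8%, and at least one of them in 78.0%. So ANCOVA alone was significant in 78.0 − 48.7 = 29.3%, and the interaction alone in 78.0 − 75.8 = 2.2%. Nearly all the disagreement is a difference in power.

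**Dilution of the group main effect.** With a sustained effect d and none at baseline, the three-visit mean differs by (0 + d + d)/3 = 2d/3, a loss of one third. At d = 0.5 the difference is 0.333. The SD of the three-visit mean is √[(1 + 2 × 0.5)/3] = 0.816, so the noncentrality is (0.333/0.816) × √15 = 1.58 and power is about 34%. For the ANCOVA average, the residual variance is 0.75 − 0.25 = 0.50, the noncentrality is (0.5/0.707) × √15 = 2.74 and power is about 76%.

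**The case against.** **This is a pilot.** Section 3.8.3 disclaims a definitive efficacy test, and family-wise error is chiefly a concern for confirmatory claims. That stands and lowers the severity. It does not remove the point, because section 3.2 still sets out to test efficacy with a directional hypothesis.

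**A condensed article may leave ranking and multiplicity to an analysis plan.** That is true of details left open. Here the article itself sets two methods in parallel and spells out the contrasts, including two that do not fit the hypothesis. The point concerns what is written.

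**The contrasts could be follow-ups to the interaction.** The stated target is change from baseline relative to control, and the interaction comes first in the power section. This is a possible reading, and under it the 8% figure, or less, is nearer the mark. But no such gate is written.

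**A stronger reading is tempting:** that the trial has a 22% false-positive rate and that its two models often disagree. The documents do not support either statement without conditions. Section 3.8.1 sets no level per contrast, so .05 for each is an inference from the power section. The 22% counts tests that are not efficacy tests. The 32% rests on an assumed effect of 0.5 SD and compares a 2-df test with a 1-df test, which address different hypotheses.

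**Conclusion.** The point holds in a limited form: the plan does not say which of its 11 between-arm tests answers the second aim. Read at .05 each, the chance of at least one false positive is about 18% over the eight efficacy-relevant tests, 22% over all 11 and 8% over the two overall tests, against about 5% for one named test. These rates are stable over the correlation structures tried.

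Discordant verdicts are common only for small to moderate true effects of an assumed sustained pattern. They mostly mean that ANCOVA detects what the interaction misses, not that the models point in opposite directions. The one-third dilution of the group main effect follows from the definition of that test whenever the effect is equal at both post-baseline visits.

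This should be fixed. Given the declared pilot purpose, it does not undermine the trial.

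**What to change.** Reword section 3.8.1 to name one primary analysis: the baseline-adjusted (ANCOVA) FN+ minus CE difference in P-PAM-MH, reported with a 95% confidence interval. The section's own rationale for ANCOVA supports this choice. Whether it is taken at one named visit or as the average of the two post-baseline visits is for the sponsor to decide, before outcome data are seen. At an assumed d = 0.5 the simulated power was about 59% for the post-intervention visit alone and 76% for the average, but the choice should also reflect which effect is of interest.

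Label the 2 x 3 ANOVA and the remaining contrasts supportive. Drop the between-arm baseline test and the group main effect that includes baseline as tests of efficacy.

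The cost is a rewording. No data or participants are lost, and the other contrasts can still be reported, but only as supportive results.

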#### Secondary outcomes

3.8.2

The secondary outcomes entail both continuous and categorical variables. For the continuous variables (subscales and total score on BTPS, and sum of discrete types of barriers), the analytic models described above will be applied. In addition, corresponding overall multivariate tests treating the outcomes as a dependent variable vector will be conducted (RM MANOVA and MANCOVA). For the parent perception of capacity after intervention items, we will use t-tests to examine perceived change and to estimate effect. For categorical items on the BTPS we will use McNemar's test.

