One proposed mechanism underlying these effects is increased parental activation. Parental activation refers to a caregiver's knowledge, skills, and confidence to effectively manage a child's mental health needs and engage with care systems on the child's behalf [28]. For example, an activated foster parent may recognize early signs of distress, ask informed questions about treatment options, advocate for evaluations or services, monitor symptoms between visits, and implement therapeutic strategies at home. Unlike parental involvement, which reflects participation in care (e.g., attending appointments), or parental education, which focuses primarily on knowledge acquisition, parental activation reflects the caregiver's capacity to take effective, goal-directed action across these domains. In pediatric and adult health settings, higher parent or patient activation has been associated with greater treatment engagement, improved adherence, and better clinical outcomes. Within child welfare settings, greater foster parent activation may facilitate earlier identification of mental health needs, more effective navigation of fragmented service systems, and more consistent treatment participation, potentially reducing placement disruptions while improving caregiver competence, satisfaction, and retention.

Building on this emerging evidence, we developed the initial prototype of *Family Navigator Plus* (*FN+,* originally named *PROACTIVE parent*), a telehealth-delivered intervention designed to increase foster parent activation in managing their foster child's mental care [26]. The current NIH-funded study includes three phases designed to further refine and pilot test FN+: 1) human-centered design workshops with foster parents, caseworkers, and providers; 2) an open trial (*N* = 12) to refine the intervention; and 3) a pilot randomized controlled trial (*N* = 60) comparing FN + to an attention control condition focused on youth civic engagement. The primary outcome is foster parent activation in the child's mental health care. The secondary outcome is overcoming barriers to treatment engagement. FN + aims to equip foster parents with sustainable skills to navigate mental health systems, respond effectively to children's mental health needs, and support treatment goals over time.

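### McNemar's test, the only analysis named for the categorical BTPS items, measures change within people and cannot compare FN+ with the control arm

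*Protocol article*

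**What the plan says.** The Introduction of the protocol article states: "The secondary outcome is overcoming barriers to treatment engagement". The instrument is the BTPS, described in Section 2.2.4 as having four subscales and carried into the randomised phase by Section 3.6.

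Section 3.8.2 divides the BTPS data in two.
- The continuous scores ("subscales and total score on BTPS, and sum of discrete types of barriers") go through the models set out for the primary outcome in Section 3.8.1: a Condition by Time repeated measures ANOVA and a baseline-adjusted ANCOVA. Multivariate versions are added: "corresponding overall multivariate tests treating the outcomes as a dependent variable vector will be conducted".
- The categorical items get a single sentence: for "categorical items on the BTPS we will use McNemar"'s test. It does not say which two of the three assessments form the pair, or whether the test is run within each arm or on both arms together.

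Section 3.4 allocates participants 1:1 to two separate arms. Section 3.1 gives the reason for the attention control: because structure and intensity are matched, "any observed differences in outcomes between groups can be attributed to the mental health"-specific content of FN+.

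**The concern.** McNemar's test asks whether, among people whose answer changed between two occasions, as many changed one way as the other. That is a question about time. The FN+ and CE participants are different, unmatched people, so no pairing links one arm to the other and the test cannot be turned into an arm comparison. Run in one arm or on both together, it mixes any intervention effect with time trends, regression to the mean and repeated questioning, which the control arm is there to remove.

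Shared change is plausible here. Under Section 3.5, CE participants also have five navigator sessions, and the content includes working with caseworkers and structured problem-solving. Some barriers could fall in both arms.

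At stake is what the pilot hands on. Section 3.8.3 wants preliminary signals of effect and inputs for planning a definitive trial. A within-person test of these items supplies no between-arm effect for either purpose.

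**Working it through.** **1. The plan's own figures.** Section 3.8.3 starts from this: "Effect sizes yielding 80% power were estimated based on a sample size of 60 subjects". With the noncentral F distribution, N = 60, correlation 0.5 and α = 0.05:
- 2x3 interaction: λ = f²·N·m·ε/(1−ρ), with f = 0.184, m = 3, ε = 0.75. Power is 0.802.
- Contrast of two times: m = 2, ε = 1. Power is 0.800.
- ANCOVA: λ = f²·N with f = 0.368 and 57 error degrees of freedom. Power is 0.800.

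All three agree with the stated 80%. No figure is given for the categorical items, so there is none to reproduce for McNemar's test.

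**2. What the test uses.** Let b be the number endorsing a barrier at baseline but not later, and c the reverse. Exact McNemar refers b to a binomial distribution with b + c trials and probability ½. Arm appears nowhere.

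**3. One expected table.** Inputs, all assumed: 30 per arm, 60% endorsing at baseline, 40% afterwards in both arms, latent normal correlation 0.5. The probability of dropping the barrier is then 0.284 and of acquiring it 0.084.
- Pooled over 60 people: b ≈ 60 × 0.284 ≈ 17 and c ≈ 60 × 0.084 ≈ 5. Endorsement goes from 36 to 36 − 17 + 5 = 24.
- Two-sided p = 2 × P(X ≤ 5 | 22, ½) = 2 × 35,443 / 4,194,304 = 0.017.
- Between arms afterwards: 12/30 against 12/30, a difference of 0.

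So the named test is significant on data in which the arms are identical.

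**4. Range of shared change.** Same assumptions, no arm effect, chance of p < 0.05 summed over all possible tables:

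| Both arms | McNemar, pooled | McNemar, FN+ only | Fisher, FN+ v CE |
|---|---|---|---|
| 60% → 60% | 3% | 2% | 3% |
| 60% → 55% | 7% | 4% | 3% |
| 60% → 50% | 20% | 9% | 3% |
| 60% → 40% | 68% | 33% | 3% |

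Comparing the two within-arm results does not rescue the approach. In the last row, McNemar is significant in FN+ but not in CE in 0.33 × (1 − 0.33) ≈ 22% of trials.

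**5. Side check on the multivariate test.** Suppose the BTPS total is the sum of its four subscales and all five scores enter one vector with the barrier count. Total minus the sum of the subscales is then zero for every participant, so the error matrix has a null direction. On simulated data for 60 people, the six-variable matrix has rank 5 and condition number about 3 × 10¹⁷. Without the total it has rank 5 of 5 and condition number about 15.

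**The case against.** The strongest reply is that the barriers outcome is already compared between arms. This stands. The subscales, the total and the barrier count all go through models with group and group-by-time terms. A reader might infer that the whole secondary outcome lacks a randomised comparison; Section 3.8.2 shows otherwise.

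A reader might also infer that the trial will claim an FN+ effect from a significant McNemar result. The article does not say so. The hypotheses in Section 3.2 concern activation and perceived capacity, not single BTPS items.

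Nor are the percentages in the table false-positive rates of McNemar's test. Where both arms really fall, the test correctly detects the fall. The figures show how often a misreading would be available, and they depend on an assumed drop: with no shared change there is nothing to misread.

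It is tempting to state outright that the multivariate test is singular. The article gives no scoring rule for the total, and its wording could be met by entering only the subscales. Prorating for missing items could leave the matrix nearly rather than exactly singular. If it were exactly singular, software would fail or drop a variable, so a silently biased result is unlikely.

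What remains does not rest on an omission. An article may leave detail to a fuller plan, but this one names a specific test for these items, and that test cannot make the comparison for which the trial randomises.

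**Conclusion.** The point holds for the categorical BTPS items and goes no further. McNemar's test is the only method named for them and cannot estimate or test FN+ against CE. This follows from the form of the test and needs no assumed rate.

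The practical size does rest on assumptions. Across shared falls of 0 to 20 points from 60%, McNemar is significant in 3% to 68% of trials pooled and in 2% to 33% in FN+ alone, with no arm effect at all. The article does not say how many BTPS items are categorical, so the share of the secondary outcome affected is unknown.

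Severity is moderate. The primary P-PAM-MH analysis, the stated power figures and the between-arm models for the continuous barrier scores are untouched, and the study is a pilot sized for feasibility. The multivariate point is a conditional side note and adds nothing to the severity.

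**What to change.** In Section 3.8.2, replace the McNemar sentence with a between-arm analysis of each categorical item at each post-baseline assessment. One option is logistic regression on arm adjusted for the baseline response, penalised where cells are sparse. Another is GEE with an arm-by-time term. Report the FN+ minus CE difference in proportions with a 95% CI. McNemar's test can stay if it is labelled as within-arm description.

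The intervals will be wide. With 30 per arm and 40% endorsing in each, the unadjusted half-width is 1.96 × √(2 × 0.4 × 0.6 / 30) = 0.25, or about 25 percentage points. For a pilot, that interval is the useful result to carry into planning the next trial.

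In the same edit, leave the BTPS total out of the MANOVA/MANCOVA vector and analyse it in its own univariate model, as already planned.

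The cost is analysis wording only. The baseline BTPS responses are already needed for the planned ANCOVA, so no new data, visits or participants are required. The change should be made before outcomes are examined by arm.
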